#### Secondary outcomes

Craving is assessed by the Transaddiction Craving Triggers Questionnaire (TCTQ) [28]. This is an instrument designed to assess what triggers craving. The questionnaire is completed at inclusion, M2, M5, and M8. Craving is also assessed using a VAS (0 to 10) at each exposure session [29] and on a monthly basis after M2, in the same way as for the primary outcome.

The frequency of hazardous drinking episodes is assessed with the AUDIT-C (Alcohol Use Disorders Identification Test) questionnaire [30], an abbreviated version of the AUDIT self-report questionnaire [31] that includes three questions about the patient's alcohol consumption. These data are collected at enrollment and at treatment phases M2, M5, and M8. Finally, reported alcohol consumption is correlated with weekly DH toxicology monitoring, if this is routinely performed at the recruiting centers. Weekly toxicology screenings for ethyl glucuronide (EtG), if performed as part of the routine care at the recruiting centers, will be recorded in the logbook.

Anxiety is assessed by the Generalized Anxiety Disorder-7 (GAD-7) questionnaire [32]. This instrument is designed to screen for generalized anxiety disorder and may also help to identify panic disorder, social anxiety disorder, and posttraumatic stress disorder. It is administered at inclusion, M2, M5, and M8.

Depression is assessed by the Patient Health Questionnaire-9 (PHQ-9) [33]. This instrument collects information on the presence and intensity of depressive symptoms. Data is collected at inclusion, M2, M5, and M8.

Self-efficacy is assessed by the Sense of Self-Efficacy Questionnaire, originally developed in German by Matthias Jerusalem and Ralf Schwarzer [34]. It is administered at inclusion, M2, M5, and M8.

Rumination is assessed by the 15-item Perseverative Thinking Questionnaire (PTQ). This is a widely used self-report measure of repetitive negative thinking [35]. It is administered at inclusion, M2, M5, and M8.

The state of presence in virtual reality is measured by the QEP questionnaire (Questionnaire sur l'État de Présence) developed by the UQO Cyberpsychology Laboratory (2002) [36, 37]. This survey is conducted at M2 for the participants randomly assigned to the VR-CET group.

Cybersickness risk is assessed after each VR-CET session using the Cybermalaise Questionnaire from the UQO Cyberpsychology Laboratory [38].

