### Sample size

To determine the number of participants needed for the study, we randomly selected 15 patients with alcohol-related disorders (AUD) who were already being treated at the Albert Chenevier Day Hospital's addiction department. Their cumulative alcohol consumption was monitored at two, five and eight months after admission to estimate the average daily consumption over eight months. The target consumption was calculated on the basis of the recommendations of the European Medicines Agency [39], aiming at a reduction of at least two risk levels according to the World Health Organization. To achieve a statistical power of 0.8, considering a risk α of 0.05 with a two-sided hypothesis, 65 patients per group are required. Assuming a drop-out rate of 20%, 78 patients per group need to be recruited, for a total of 156 patients for both groups. See Table 2 for recruitment procedure.

**Table 2 Tab2:** Recruitment procedures

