### Statistical methods

The characteristics of all patients will be described globally and according to their randomization group, using the number of patients (%) for qualitative variables and the median [interquartile range] or mean (± standard deviation) for quantitative variables, depending on the normality of their distribution. A patient flow diagram will be generated. Results are reported according to CONSORT recommendations. Tests will be two-tailed, and a significance level of *p* < 0.05 will be considered statistically significant. The primary outcome (self-reported cumulative number of standard drinks consumed at 8 months) will be compared between the two groups using Student's t-test for independent samples. Complementary analyses will be conducted using generalized linear regression models adjusted for minimization factors and number of sessions per setting. Given the repeated measurement of outcomes and the multicenter design of the study, additional analysis will be performed including Cox and mixed models. To consider Survival analysis will also be conducted using a linear mixed model. Secondary endpoints will be analyzed using the same methodology as for the primary endpoint, i.e. a comparison of the mean using the usual tests. primary endpoint, i.e. a comparison of means using standard tests at 8 months. Secondary analyses to assess changes in secondary endpoints will be performed using evaluated using linear mixed models.

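### Six secondary scales have a pre-randomisation score, but their main between-arm comparison is an unadjusted test of M8 means: valid, yet less precise than a baseline-adjusted one

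*Protocol article*

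**What the plan says.** The protocol article (Statistical methods) compares the primary outcome between arms with an independent-samples Student's t-test and carries that approach over: "Secondary endpoints will be analyzed using the same methodology as for the primary endpoint, i.e. a comparison of the mean using the usual tests". The next fragment, which partly repeats this sentence, supplies the time point: "primary endpoint, i.e. a comparison of means using standard tests at 8 months". Neither names a covariate. The complementary regression described for the primary outcome adjusts for the minimisation factors and the number of sessions, not for a baseline score. The section ends with linear mixed models for change in the secondary endpoints, labelled as secondary analyses.

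The Secondary outcomes section gives the schedule. For TCTQ: "The questionnaire is completed at inclusion, M2, M5, and M8". GAD-7, PHQ-9, self-efficacy and PTQ follow the same schedule, and AUDIT-C is taken at enrolment, M2, M5 and M8. The Treatment groups section places randomisation at M1, after the four group CBT sessions that both arms share. The inclusion scores therefore precede allocation.

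The Sample size section concerns the primary outcome only: "To achieve a statistical power of 0.8", "considering a risk α of 0.05 with a two-sided hypothesis, 65 patients per group are required".

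**The concern.** A score taken before randomisation on the same scale is usually the strongest available predictor of the later score. Using it as a covariate removes outcome variation unrelated to treatment. Here it exists for all six scales that carry the named secondary objectives or the drinking-episode measure, but the leading comparison leaves it out.

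At stake is the chance of detecting a real difference in craving, anxiety, depression, rumination or self-efficacy, and the width of the confidence intervals for those differences. The trial was sized on drinks consumed, so nothing in the plan secures precision for these scales. That makes an available gain in precision worth taking.

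**Working it through.** **Inputs from the article.** Two-sided α = 0.05, power 0.80 and 65 evaluable patients per group (Sample size, primary outcome). Comparison of means at M8 (Statistical methods). Inclusion scores for six scales (Secondary outcomes). Randomisation at M1 (Treatment groups).

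**Input not in the article.** The correlation r between the inclusion and M8 scores. I assume 0.3 to 0.7.

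**The plan's own figure.** The 65 per group cannot be rebuilt, because the article gives neither the target difference nor the SD. It can only be inverted. The standardised difference with 80% power at 65 per group is

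d = (1.960 + 0.842) × √(2/65) = 2.802 × 0.1754 = 0.491 (normal approximation; 0.495 by the t distribution).

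This d belongs to the primary outcome. I use it below only as a reference effect that an unadjusted test would detect with 80% power.

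**Effect of adjustment.** Adjusting for the inclusion score multiplies the outcome variance by (1 − r²). The standard error is multiplied by √(1 − r²), and the unadjusted variance is 1/(1 − r²) times the adjusted one. Approximate power is Φ(2.802/√(1 − r²) − 1.960).

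| r (assumed) | 1 − r² | SE multiplier | Unadjusted/adjusted variance | Power at 65 per arm | n per arm for 80% |
|---|---|---|---|---|---|
| 0.3 | 0.91 | 0.954 | 1.10 | 83.6% | 60 |
| 0.5 | 0.75 | 0.866 | 1.33 | 89.9% | 49 |
| 0.7 | 0.51 | 0.714 | 1.96 | 97.5% | 34 |

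Example at r = 0.5: 2.802/0.866 = 3.235; 3.235 − 1.960 = 1.275; Φ(1.275) = 0.899.

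**Simulation check.** With 4,000 runs and 65 per arm, unadjusted versus adjusted power was 79.7% vs 82.4% (r = 0.3), 79.9% vs 90.1% (r = 0.5) and 78.8% vs 97.1% (r = 0.7), in line with the formula.

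**Chance imbalance.** The standard error of a baseline difference at 65 per arm is √(2/65) = 0.175 SD, so differences up to about 1.96 × 0.175 = 0.34 SD are ordinary. The share carried into the unadjusted M8 difference is about r times that. At r = 0.5 this is 0.5 × 0.34 = 0.17 SD.

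**The case against.** The best defence is that nothing is invalid. Under randomisation the unadjusted M8 test is unbiased and keeps its type I error, and its standard error already reflects chance baseline differences. The endpoints are secondary, and a longitudinal analysis is planned alongside. All of that stands, and it limits the point to efficiency.

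A reader might infer several stronger things that the article does not support:

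- **That every secondary scale has an inclusion value.** No inclusion value is stated for the craving VAS. The presence and cybersickness questionnaires are taken only in the VR-CET arm, during or after exposure, so they have no between-arm comparison.
- **That the plan discards baseline altogether.** The mixed models of change can use the inclusion scores. Baseline is missing from the main test, not from the plan. How it enters the mixed model is a detail that an analysis plan may settle.
- **That the two analyses have no order.** The mixed models are called secondary, so the M8 test leads.
- **That the M8 test is the least precise valid choice.** An unadjusted change score has 2(1 − r) times its variance if SDs are equal at both visits: 1.4 at r = 0.3, so less precise whenever r is below 0.5.
- **That a baseline imbalance passes in full into the M8 difference.** Only about r times it does.
- **That the minimisation factors are certainly excluded.** The carry-over sentence is garbled, and it could be read as including the complementary adjusted regression.

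The size is also open to challenge. Inclusion precedes M8 by eight months and randomisation by a month of shared CBT, which may lower r. At r = 0.3 the gain is modest.

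**Conclusion.** The point holds as an efficiency recommendation limited to six scales: TCTQ, AUDIT-C, GAD-7, PHQ-9, self-efficacy and PTQ. The leading comparison is valid but has about 10%, 33% or 96% more variance than a baseline-adjusted one at r = 0.3, 0.5 or 0.7. The direction does not depend on r, apart from the negligible loss of one degree of freedom when r is near zero; the size depends on it entirely, and r may differ between scales. The results assume a roughly linear relation between the inclusion and M8 scores with the same slope in both arms.

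The power figures are illustrations. They start from an effect back-solved from the primary outcome's sample size and should not be read as planned power for any secondary scale. The primary conclusion is unaffected.

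**What to change.** In Statistical methods, name one baseline-adjusted model as the main between-arm analysis for each of the six scales. Either of these would do:

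- ANCOVA of the M8 score on arm, inclusion score and minimisation factors; or
- the mixed model already planned, fitted to M2, M5 and M8 with arm, visit, arm-by-visit interaction, inclusion score and minimisation factors, and reporting the arm contrast at M8.

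Keep the unadjusted M8 means by arm as a descriptive display. Scales without an inclusion value need no change on this account. The duplicated sentence on secondary endpoints can be cleaned up in the same edit.

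The cost is a few lines of wording, fixed before the data are analysed. No new measurement, visit or patient is needed.

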### Methods for accounting for missing, unused, or invalid data

Patients who withdraw consent or discontinue follow-up during the study are not replaced. Missing data will be systematically searched for and checked in the patients' medical records. Analyses may be performed after imputation of missing data. Missing data will be handled using multiple imputation as recommended by the National Research Council Panel on Handling Missing Data in Clinical Trials [40].

### Selection of participants for analyses

The intention-to-treat population will include all patients who signed the informed consent form and were randomized to one of the two study arms and will be analyzed according to the initial randomization group. The per-protocol (PP) population will include patients enrolled in the study without major deviations from the current protocol, including erroneous inclusion of patients, changes or noncompliance with the treatment assigned at randomization. The primary endpoint will be analyzed by ITT and secondarily by PP analyses. PP analyses. Secondary endpoints will be analyzed according to ITT and PP principles to ensure robustness of results.

### Data monitoring

Two committees work together to monitor the data and guide the research.i) The Steering Committee meets quarterly. Its purpose is to define the general organization, determine the methodology, monitor the progress of the research, coordinate information, initially determine the methodology, validate the applications of persons recruited under the protocol, and define any relevant modifications to the protocol necessary for the continuation of the trial. At the end of the meeting, the sponsor will be informed of any decision that requires rapid action by the sponsor.ii) The Scientific Committee meets quarterly. Its purpose is to define the objectives of the protocol, to draft the protocol and to propose modifications during the research. Decisions taken at these meetings are validated after discussion and majority vote.

### Audit

All data, documents and reports may be audited without invoking medical confidentiality. Audits can be carried out at any stage of the research process, by independent persons appointed by the sponsor. The aim is to guarantee the quality of the research, the validity of the results, and compliance with applicable laws and regulations.

### Ethics and dissemination

#### Research ethics approval

This research is conducted in accordance with the World Medical Association's Declaration of Helsinki. The study was approved by the French ethic committee (Comité de Protection des Personnes Sud-Est VI) on 07/07/2023 (National ID 2022-A02797-36). Any substantial modification of the protocol by the coordinating investigator must be approved by the sponsor. Once approved, the sponsor must obtain a favorable opinion from the ethic committee before implementation.

#### Consent or assent

Patients in addictology DH receive initial information from a trained investigator. Informed consent is obtained by the principal investigator, an attending physician, or a qualified person, with a two- to four-week cooling-off period. The investigator documents participation in the patient's medical record, retains a copy of the consent form, and a tamper-proof envelope is archived by the sponsor at the end of the study. No exclusion period is defined at the end of participation. No anticipated harm or compensation to subjects is foreseen, as the research will be organized as part of their routine care. However, participants in the CBT group will be offered the opportunity to receive virtual reality exposure sessions as part of their routine care once participation in the study has ended.

#### Confidentiality and access to data

Quality control personnel ensure confidentiality, making data non-identifiable, using initials and a coded ID. The sponsor ensures that each participant has given written consent to access data. APHP Cleanweb® data will be stored on dedicated servers. Physical documents will be kept in a locked cabinet during the research, then archived in accordance with regulations. Documents specific to minimal-risk research will be archived by the investigator and sponsor for 15 years after the end of the research, including sealed envelopes, files, successive versions of the protocol, ethic committee opinions, correspondence, inclusion list, special appendices, final report, and documents relating to data collection. Study results will be communicated to investigators at all centers, to patients and to the scientific community in general. APHP is the owner of the data. Additionally, a contract has been established with the University of Nanterre. This agreement allows for further statistical analyses to be conducted in collaboration with the CLIPSYD laboratory from the Faculty of Psychology at the University of Nanterre, under the direction of [name]. For this purpose, pseudonymized research data will be securely transmitted to the team to facilitate these analyses. All data necessary to support the protocol can be provided upon request to APHP.

## Discussion

The present study aims to evaluate the efficacy of VR-CET combined with CBT in the treatment of AUD in recently abstinent individuals. A recent review of the literature highlights the emergence of virtual reality as an innovative and promising tool in the therapeutic landscape [21]. Studies on the efficacy of VR-CET have mainly focused on craving, with findings such as that exposure to alcohol-related stimuli in virtual reality can increase participants' desire to drink [5]. In terms of its reduction, VR-CET appears to have positive effects, particularly for individuals with AUD [1, 41]. The perceived level of realism of the virtual environment seems to influence this efficacy, with a more pronounced reduction in the desire to drink when the environment is perceived as realistic. About anxiety, the effects of VR-CET were mixed, but integration with CBT resulted in a significant reduction in post-treatment anxiety, although less favorable than in the CBT group alone. About alcohol use, only one study examined this variable and showed that VR-CET had no significant short-term effects [42]. The systematic review highlighted the lack of longitudinal data to consolidate the efficacy of VR-CET as a therapeutic tool to reduce alcohol consumption Table 2.

Our protocol aims to address the limitations of previous research by increasing the sample size (*N *= 156), by aiming not only for abstinence but also for a reduction in consumption, which seems more realistic, by having broad inclusion criteria to allow the inclusion of a population as close as possible to clinical reality, integrating sociodemographic questions into our inclusion questionnaire, and considering comorbidities via the MINI questionnaire at inclusion. In addition, we included urinary toxicity test (ethyl glucuronide) during the two months of therapy to objectify alcohol use data. In response to previous criticism regarding the lack of virtual environments with negative connotations, two neutral environments (subway and supermarket) were included to induce a sense of stress.

Despite these improvements, several limitations must be considered. We did not include the multisensory aspect, in particular olfactory stimulation, which could potentially influence perception of the realism of virtual environments. Furthermore, we did not include objective data such as heart rate or urinary toxins about craving and alcohol consumption, only declarative data are collected, leaving a gap in our understanding of physiological responses to alcohol-related stimuli and on subjects' actual consumption. 

Despite the limitations of our study, *E-Reva* contributes to the literature on the use of VR in the treatment of AUD. These findings could potentially open significant horizons for future patient interventions. VR is emerging as an innovative therapeutic resource that provides a unique setting for exposure to alcohol-related environments. Integrating VR into the treatment of AUD requires a thoughtful approach that considers the specific nuances of this disorder. Personalizing interventions based on a thorough understanding of individual patient needs remains critical to maximizing the therapeutic efficacy of VR. Overall, the steady progress of research in this field promises significant advances. These advances will not only strengthen our understanding of the efficacy of VR in the treatment of AUD but will also open new perspectives for innovative therapeutic interventions focused on the specific needs of patients. Thus, VR is emerging as a promising tool to enrich the therapeutic landscape and pave the way for a more targeted and effective approach to the treatment of AUD.

### Trials status

The study began enrolling participants in October 2023, and recruitment is scheduled to end in October 2025. Protocol version 1.0, 12/05/2023.

## Data Availability

The data sets analyzed in the current study and the statistical code are available from APHP and the principal investigator on reasonable request, as is the full protocol.

## Abbreviations

AUD: Alcohol use disorder
AUDIT: Alcohol Use Disorders Identification Test
CBT: Cognitive behavioral therapy
CET: Cue exposure therapy
DH: Day hospitals
DSM: Diagnostic and Statistical Manual of Mental Disorders
GAD-7: Generalized Anxiety Disorder 7
PP: Per-protocol
PTQ: Perseverative Thinking Questionnaire
QEP: State of Presence Questionnaire
TCTQ: Transaddiction Carving Triggers
TLFB: Timeline Followback
VAS: Visual analog scale
VR: Virtual reality
VR-CET: Virtual reality cue exposure therapy
